#### Missing data {20c}

We will analyse by intention to treat. In the (extremely unlikely) event that some participants withdraw before complete healing and that rate differs between groups, a sensitivity analysis will be applied. We will explore the patterns and extent of any missing data, particularly those relating to the two main endpoints. We do not plan to impute missing values, but may consider the use of multiple imputation or other strategies within the sensitivity analysis if necessary.

#### Methods for additional analyses {20b}

##### Quality of life

Quality of life (QoL) will be analysed by calculating and comparing area under the curve (AUC) across intervention and controls. Baseline results will be triangulated with clinical observations to avoid bias and to determine how differences in healing rates correspond to differences in quality of life end-points.

##### Activity measurement

We will also compare average daily step count between treatment and control groups as a simple difference in means (t test). Since one group may stay longer in hospital than the other and since there may be an interaction between rate of healing and step count, we will compare step counts over periods pre-set at 7, 14 and 42 days.

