#### Activity measurement

All participants will be invited to wear a pedometer (Model: Mi Smart Band 5, Model: XMSH10HM) on the ankle of their non-affected limb (or non-index case affected limb) which they will wear from the first dressing change until 42 days (the point where cross-over may occur) or discharge, whichever comes first. This will act as a proxy measure of weight bearing and enable us to monitor activity across intervention and control groups and thereby evaluate whether the level of activity is similar across groups.

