#### Sample size {14}

Sample size is based on the two primary outcomes: rate of healing and time to complete re-epithelialization. On the latter, we assume that 70% of ulcers will heal within 42 days with standard care [21]. Further, assuming that the intervention will increase this proportion to 90% and hazards are constant and proportional, for a two-sided test of the hazard ratio with a type I error of 5% and statistical power of 80% and a 1:1 allocation ratio, 47 individuals are required in each group. To allow for withdrawals and right censoring, we aim to recruit 65 patients in each group. We expect rate of healing to provide yet more precise estimates.

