## Discussion

This protocol describes an individually randomised control trial to evaluate a treatment using autologous blood products L-PRF, to promote ulcer healing in leprosy. Despite the promising anecdotal evidence regarding this treatment, high-quality, empirical data are currently unavailable [12, 14].

Most of the evidence on ulcer healing, including the Cochrane review [12], is based on proportion of ulcers healed (completely epithelialized) by 42 days. This is sub-optimal because complete epithelialisation is a clinical decision that is also used to decide on discharge. This provides an opportunity for observer (outcome) bias. For this reason, we will measure rate of healing. These measures are all made centrally (in Birmingham) by two observers who are ‘blind’ to intervention status.

Activity measurements are not a primary outcome measure in our study. However, by collecting step-count daily and over the course of the inpatient stay over the periods specified above, we can exclude activity as a confounding factor in any differences found in ulcer healing rates between intervention and control groups.

We are also planning to do a range of nested studies. Given sufficient time and resources, we hope to video tape a subset of dressing changes (five intervention and two controls selected at random in Birmingham) as a means of photograph supervision and for additional quality control. We will also develop a more detailed health economics protocol. Finally, we will develop follow on studies based on the results of the trial.

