We are using three methods to measure the rate of ulcer healing and time to complete re-epithelialisation. Readers might wonder at such an extensive set of methods and consider this ‘overkill’. Our rationale for using these multiple ulcer measurement methods is two-fold. First, it is crucially important in our judgement to create a situation where results cannot be explained away by measurement error (for all that measurement error is more of a threat to precision than to accuracy). Second, we wish to contribute to the methodological literature on ulcer measurement. As investigators we hope that the results will be consistently null or positive (or even negative). However, we realise that we may end up with results that toggle around the conventional statistical threshold , say, according to ulcer measurement method or whether or not adjustment had been carried out for any discrepancy in ulcer size at base-line. In that case, we will simply report the different results and allow the reader to make an interpretation. We will not (miss) use statistical tests as decision rules.

By using a randomised control method, alongside standardised blindly assessed photographs, and information on activity, this research will provide robust evidence on the clinical and cost-effectiveness of L-PRF in the treatment of leprosy ulcers. Data collection and ulcer assessment follows a ‘closed-loop’ such that the photograph and image can follow only one pathway from camera to completed measurement. An additional benefit is the evaluation of the effects of treatment on quality of life for people living with the effects of leprosy. The findings will also be relevant to other ulcerative conditions, particularly diabetes, where ulcers similarly result from peripheral nerve damage. The results will improve our understanding of the scalability of this treatment across low-income countries for ulcer healing in leprosy and other similar conditions.

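### The Discussion says step counts let the trial exclude activity as an explanation, but the only stated analysis, a t test of no difference, cannot establish similarity

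*Protocol article*

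**What the plan says.** Three places in the protocol article bear on this.

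- **Purpose.** The Activity measurement paragraph under Intervention says that a pedometer, which participants are invited to wear, will allow the team to "evaluate whether the level of activity is similar across groups".
- **Method.** The Activity measurement paragraph under Methods for additional analyses {20b} says the team will "compare average daily step count between treatment and control groups as a simple difference in means (t test"). Because length of stay may differ between arms, "we will compare step counts over periods pre-set at 7, 14 and 42 days".
- **Conclusion.** The Discussion says that, by collecting step counts over these periods, "we can exclude activity as a confounding factor in any differences found in ulcer healing rates between intervention and control groups".

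The same Discussion paragraph also says "Activity measurements are not a primary outcome measure in our study". The adjusted healing analyses name trial ulcer area and age as covariates (Outcomes {12}; Statistical methods for main endpoints {20a}). No stated analysis of healing uses step count.

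**The concern.** The purpose is a question about similarity, the method tests for a difference, and the conclusion is that activity is ruled out. The method does not lead to the conclusion. Failing to reject a null of no difference is not evidence of similarity, and it becomes more likely as the data become fewer or noisier. Poor pedometer uptake would therefore make an apparently reassuring result easier to obtain.

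The point matters because participants and the staff who change dressings know the allocation, and the article itself says that weight bearing and activity are adversely associated with healing of plantar ulcers. If the arms rest to different degrees, that could contribute to a healing difference or mask one. A reader who takes the Discussion at its word would believe this had been ruled out when the planned comparison could not rule it out.

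**Working it through.** **Inputs from the protocol article**

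- Sample size {14}: "we aim to recruit 65 patients in each group". The number required before allowing for withdrawals and censoring is 47 per group.
- The sizing is "for a two-sided test of the hazard ratio with a type I error of 5% and statistical power of 80% and a 1:1 allocation ratio", with 70% versus 90% healed at 42 days. It concerns time to healing only; nothing is sized for step count.
- No step-count SD and no negligible difference are given, so differences *d* and margins *m* below are in SD units.

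**The plan's own figure first**

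Under constant proportional hazards, HR = ln(0.10)/ln(0.30) = 1.912. Schoenfeld's formula gives 4 × (1.960 + 0.842)² / (ln 1.912)² = 74.7, so 75 events. With a mean event probability of (0.70 + 0.90)/2 = 0.80, this is 75/0.80 = 93.75 participants, or 47 per group. The stated figure reproduces.

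**Precision of the step-count comparison**

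Standard error of the difference = √(2/n). The 95% half-width uses t(0.975) on 2n − 2 degrees of freedom.

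- n = 65: SE = 0.175; half-width = 1.979 × 0.175 = 0.35 SD.
- n = 47: SE = 0.206; half-width = 1.986 × 0.206 = 0.41 SD.

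**Chance that a real difference is non-significant**

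P(|T| < t(0.975)), with T non-central t and non-centrality d × √(n/2), two-sided 5%, every participant contributing data:

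| True difference | 65 per arm | 47 per arm |
|---|---|---|
| 0.2 SD | 0.80 | 0.84 |
| 0.3 SD | 0.60 | 0.70 |
| 0.5 SD | 0.19 | 0.33 |

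By the normal approximation, the difference detectable with 80% power is (1.960 + 0.842) × SE: 0.49 SD at 65 per arm and 0.58 SD at 47.

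**What a formal similarity claim would require**

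The chance that the whole interval lies within ±m when the true difference is zero is max(0, 2Φ(m/SE − z) − 1), with z = 1.960 for a 95% interval and 1.645 for a 90% interval. At 65 per arm:

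| Margin | m/SE | 95% CI inside | 90% CI inside |
|---|---|---|---|
| 0.3 SD | 1.71 | 0% | 5% |
| 0.4 SD | 2.28 | 25% | 47% |
| 0.5 SD | 2.85 | 63% | 77% |

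A margin of 0.3 SD is narrower than the 95% half-width of 0.35 SD, which is why it is essentially out of reach.

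**The case against.** A reader might infer that the trial will report activity as excluded whenever p > 0.05, and as imbalanced whenever p < 0.05. The article states no such rule. It names the difference in means first and the t test in brackets, and that analysis yields a confidence interval directly. The Discussion also says "We will not (miss) use statistical tests as decision rules". That sentence concerns the ulcer results, so it does not withdraw the claim about activity, but it does count against assuming a p-value rule.

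A reader might also infer that the lack of an equivalence margin is itself a defect. It is not. An analysis plan that is not shown may hold such detail, and step count is a supportive measure outside the listed primary and secondary end-points. Asking whether activity is similar leaves either answer open and does not commit the trial to a formal equivalence test.

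Nor do the documents support the reading that the efficacy result is at risk. The healing comparisons are by intention to treat and do not use step count. Steps are recorded from the first dressing change and so, on the stated sequence, after allocation. A between-arm difference caused by allocation would lie on the path from treatment to healing, so it would be a mediator rather than a confounder.

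All of this stands and narrows the point. It does not rescue the sentence in the Discussion, which promises exclusion before any data are seen and for which the t test is the only stated basis.

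**Conclusion.** The point holds as a mismatch between a stated conclusion and the method offered for it. At the planned 65 per arm, even with complete data, a true activity difference of 0.3 SD would be non-significant about 60% of the time, and the 95% interval would span about 0.35 SD on each side. Such a comparison cannot by itself exclude activity as a contributor to a healing difference.

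The figures assume roughly normal means, equal variances and a step count from every participant. Pedometer wear is by invitation, so fewer participants may contribute and precision would then be lower; 47 per arm serves as an illustration. How many steps 0.3 SD represents, and whether that would matter for healing, cannot be said from the documents.

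The consequence is confined to interpretation. It is worth correcting because the repair is cheap, but it does not threaten the primary analyses.

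**What to change.** 1. **Methods for additional analyses {20b}, Activity measurement.** Report the between-arm difference in mean daily steps with its 95% confidence interval for each of the 7-, 14- and 42-day windows, and base inference on that interval instead of the t-test p value.
2. **Discussion.** Replace the exclusion claim with wording such as: *The trial will report the range of between-arm activity differences compatible with the data. A non-significant difference will not be taken as evidence of similarity. Because activity is measured after randomisation, it may be a mediator of any healing difference.*
3. **Only if a claim of similarity is wanted.** Set a margin before unblinding, justify it, and require the confidence interval to lie inside it, stating the confidence level. The investigators must choose the margin; the documents support no particular value.

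The change needs no new data or participants. Its cost is a weaker activity statement that will often be inconclusive: under option 3 with a 95% interval and a margin of 0.4 SD, similarity would be shown only about a quarter of the time even if the arms were truly identical.

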##### Economic evaluation

An economic evaluation of L-PRF will be undertaken. The model will estimate the impact of L-PRF on net population health in terms of daily and quality adjusted life years (QALYs/DALY) over a long-term time horizon. The effectiveness of the treatment will be reflected by estimating the statistical relationship between the primary end-point in the efficacy trial and HRQoL (health-related quality of life) based on participants’ completion of the generic quality of life instruments. This analysis will also reflect other characteristics of participants that are potentially prognostic and predictive of the efficacy of L-PRF. The analysis will provide a careful assessment of how the cost-effectiveness of L-PRF varies according to its local acquisition cost, as well as other parameters that could vary between localities. Full uncertainty analysis will be undertaken to establish whether there is sufficient evidence to support local funding of L-PRF at a given acquisition cost or whether additional evidence generation is necessary and worthwhile. We shall develop the model before the data to populate it are available and our work-plan will included a review of the relevant literature in countries with both high and low incomes.

##### Reporting

Where a participant withdraws from the intervention as a whole, no further data will be collected. Where the participant withdraws from the randomised intervention but agrees to contribute data, they will be followed-up to the point of discharge as an inpatient. The trial will be reported in line with the CONSORT (Consolidated Standards of Reporting Trials) Standards [27, 28].

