### Trial design {8}

A single-centre, prospective, single blinded, parallel group, 1:1 individually randomised controlled trial. Study duration is 48 months (maximum). Participants and practitioners will not be blinded, but the assessors will be completely blinded, as we describe in the section on ulcer measurements. Each participant will be followed up for up to 6 months from the point of randomisation. Consent (see ethics) and baseline data collection will precede randomisation. A summary of the study pathway is shown in Fig. 1.

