#### Outcomes {12}

The main end-points will be:
‘Rate of healing’ based on two observations per week of ulcer size censored at 42 days (cm^2^ per unit time). We will estimate the effect of the intervention on the change in the ulcer size per unit time, i.e. the rate of healing (see Statistical Analysis).Time to complete re-epithelialization (right-censored at 42 days).

Both end-points will be analysed with and without adjustment for baseline characteristics (trial ulcer area and participants’ age), but we prefer unadjusted outcomes in randomised studies and therefore declare them as ‘primary’.

Secondary end-points:
Rate of healing based on two observations per week up to 70 days (cm^2^ per unit time) (calculated as described below).Time to complete re-epithelisation (observed up to 70 days).Generic quality of life (QoL) measured at first dressing change, fortnightly during in-patient stay and at 6-month follow-up, using the EQ-5D 3L. This scale has previously been used and validated in a Nepali population [17]. As far as we are aware, there is no valuation tariff in the Nepalese population, although this may change by the time that the analysis starts. Therefore, we propose not to prespecify the tariff but instead select the tariff at a later date. We note that tariffs are currently available for nearby countries including Sri Lanka [18] and China [19, 20].Longer-term outcomes measured at 6-month follow-up from randomisation will be proportion with:
i.Recurrence of treated ulcer;ii.Appearance of new ulcer;iii.Anatomical changes in the limb;Days hospitalised prior to discharge and total (to include any readmission due to leprosy/ulcers) by 6 months.Health economic information:
i.Number of visits to any healthcare facility from discharge to the end of follow-up at 6 months.ii.Data on the time taken to change dressings at the twice weekly changes.

Rate of healing will be assessed from blindly assessed photographs (Fig. 2). However, as complete healing may trigger discharge, we will monitor for cases discharged before the blinded assessor in Birmingham has noted complete re-epithelization.

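### Participants who stop the allocated treatment but still agree to give data are followed only to discharge, so their 6-month secondary outcomes are lost by rule and cannot be analysed in full by intention to treat

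*Protocol article*

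**What the plan says.** The Reporting section of the protocol article describes two kinds of withdrawal. For the first, "Where a participant withdraws from the intervention as a whole, no further data will be collected". For the second, where the participant leaves only the randomised treatment and "agrees to contribute data, they will be followed-up to the point of discharge as an inpatient", observation ends when the participant leaves hospital. This point concerns the second group.

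Other sections describe a longer horizon:

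- Trial design {8}: "Each participant will be followed up for up to 6 months from the point of randomisation".
- Outcomes {12}: "Longer-term outcomes measured at 6-month follow-up from randomisation will be proportion with" recurrence, a new ulcer or anatomical change in the limb. The same section places an EQ-5D 3L measurement at 6 months, counts total hospital days including readmissions to 6 months, and counts healthcare visits from discharge to 6 months.
- Plans for assessment and collection of outcomes {18a}: a 6-month assessment by outpatient appointment or home visit, with no exception for people who stopped treatment.
- Missing data {20c}: "We will analyse by intention to treat", not limited to particular endpoints, and "We do not plan to impute missing values, but may consider the use of multiple imputation or other strategies within the sensitivity analysis if necessary".

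**The concern.** An intention-to-treat comparison needs outcomes on everyone randomised, whatever treatment they went on to receive. Here the data-collection rule itself removes 6-month outcomes from people who stopped treatment and were willing to be seen again. This is not ordinary loss to follow-up.

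People who stop may differ in prognosis from those who continue. If so, the 6-month proportions among those still followed no longer estimate the proportions in the randomised groups. The outcomes at stake show whether healing lasts (recurrence, readmission) and supply post-discharge resource use for the economic evaluation, which is a stated objective.

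The loss may also be uneven between arms. Up to 80 ml of blood is drawn twice weekly in the L-PRF arm and none in the control arm. Those who withdraw go on to usual care, which is already the control treatment. It is therefore mainly L-PRF participants who have an allocated treatment to stop.

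**Working it through.** **1. Does the rule touch the sample size?** Inputs from Sample size {14}: 70% healed by 42 days on control, 90% on L-PRF, constant proportional hazards, two-sided 5%, 80% power, 1:1 allocation.

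- Hazard ratio = ln(1 − 0.90) / ln(1 − 0.70) = 1.912.
- Events (Schoenfeld) = 4 × (1.960 + 0.842)² / (ln 1.912)² = 74.7, rounded up to 75.
- Participants = 75 / 0.80 = 93.75, or 46.9 per group, rounded up to 47.

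The protocol's 47 per group is reproduced. It rests on the 42-day endpoint only, so the follow-up rule leaves both 47 and 65 unchanged.

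**2. Which outcomes are lost for a consenting participant who stops treatment?**

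| Outcome | Collected | Under the Reporting rule |
|---|---|---|
| Rate of healing and time to healing, 42 days (primary) | Inpatient stay | Kept |
| Rate of healing and time to healing, 70 days | Inpatient stay | Kept |
| EQ-5D 3L, first dressing change and fortnightly | Inpatient stay | Kept |
| EQ-5D 3L at 6 months | 6-month visit | Lost |
| Hospital days before discharge | Inpatient stay | Kept |
| Total hospital days with readmissions | To 6 months | Lost |
| Dressing-change time | Dressing changes | Kept |
| Healthcare visits after discharge | To 6 months | Lost |
| Recurrence, new ulcer, limb changes | 6-month visit | Lost |

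**3. How many people?** The protocol gives no discontinuation rate. Assuming that 5%, 10% or 20% of 65 L-PRF participants stop and still agree to give data, 65 × 0.05 = 3.25, 65 × 0.10 = 6.5 and 65 × 0.20 = 13 would have no 6-month outcome.

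**4. What could that do to a 6-month proportion?** Let p be the true proportion in the arm, q the proportion among those who stop, and d the fraction stopping. The proportion observed among the rest is (p − d·q) / (1 − d). With p = 30% and q = 50%, both assumed:

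- d = 5%: (0.30 − 0.025) / 0.95 = 28.9%, about 1 point too low.
- d = 10%: (0.30 − 0.05) / 0.90 = 27.8%, about 2 points too low.
- d = 20%: (0.30 − 0.10) / 0.80 = 25.0%, 5 points too low.

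If this happened only in the L-PRF arm, the error would favour L-PRF. If q = p there is no bias. If q is below p the sign reverses: with q = 10% and d = 10%, (0.30 − 0.01) / 0.90 = 32.2%, about 2 points too high.

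**The case against.** The strongest reply is that little of importance is affected. Both primary endpoints stop at 42 days (rate of healing is "based on two observations per week of ulcer size censored at 42 days"), and consenting participants who stop treatment are still observed until discharge. They can be analysed as randomised, and are censored only if they leave before healing or day 42, as anyone else would be. This stands. A reader might infer that the whole intention-to-treat analysis is impossible, but the documents do not support that.

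A reader might also infer that every economic input is lost. It is not: the economic model relates the primary endpoint to quality of life, and inpatient data on both are kept, as is dressing time.

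The group may be very small. No rate is stated, and the gap between 47 and 65 per group (18 of 65, or 27.7%) covers withdrawals and right censoring together, so it does not forecast how many will stop. That the loss falls mainly on the L-PRF arm is inferred from the blood draws and the care given after withdrawal; the protocol does not state it.

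It is tempting to add that the sensitivity analysis is badly triggered, because it applies in the "event that some participants withdraw before complete healing and that rate differs between groups, a sensitivity analysis will be applied". I do not press this. If loss were one-sided the trigger would fire. The same section also undertakes, without condition, to explore missing-data patterns, and the details may sit in an analysis plan that is not shown.

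Two questions of scope remain. The Trial design sentence gives 6 months as a maximum, so the conflict there is softer than with the Outcomes and assessment sections. The Reporting rule speaks of participants who withdraw; whether it covers discontinuation decided by the local investigator is unclear.

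None of this removes the core point. The early end of follow-up is a stated rule and not something a condensed article has merely omitted.

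**Conclusion.** The point holds for the 6-month secondary outcomes only. For participants who leave the randomised treatment but agree to give data, the Reporting rule discards those outcomes, so they cannot be analysed on everyone randomised as the Missing data section implies. The Reporting section also needs reconciling with the Trial design, Outcomes and assessment sections. The primary and 70-day healing analyses are largely unaffected, and no stated figure changes.

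The size cannot be determined from the document. Errors of 1 to 5 points in a 6-month proportion rest on assumed stopping rates of 5% to 20% and an assumed 20-point difference in risk between those who stop and the arm as a whole. The direction depends on who stops, and an imbalance between arms is plausible but not established. It is worth correcting because the correction is cheap.

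**What to change.** Reword the Reporting section so that everyone who stops the allocated intervention, for whatever reason, but still consents to data collection is followed through the planned 6-month clinic or home visit and analysed in the randomised group. Reserve the end of data collection for those who withdraw consent to it. Align Trial design {8}, Outcomes {12}, Plans for assessment {18a} and Missing data {20c} with that wording.

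No participant would then lose 6-month data by rule, although ordinary loss to follow-up would remain. The change concerns data collection only and leaves treatment and clinical care as they are. It costs a few more 6-month visits; the clinic or home visit and the participant cell phones for arranging it are already described in the protocol.
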